### Statistical analyses

Primary outcomes for HLaC implementation will be reported descriptively. Analyses of secondary (effectiveness) outcomes will be by mixed models, which allow for repeated measures (baseline and follow-up) and will include all participants with baseline data (including those with missing data at follow-up) with adjustment for predictors of dropouts to minimise non-response bias. Data will be analysed collectively (pooled) across Cancer Councils as well as reported individually for each. To minimise type I errors because of testing multiple outcomes, significance will be set at *p* < 0.001 (two-tailed). Sensitivity of conclusions to missing data assumptions will be evaluated.

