### Sample size related to secondary (effectiveness) outcomes

Given the resources available in each Cancer Council to support HLaC implementation, the service delivery is expected to provide a sample size of approximately 900 participants across the four participating Cancer Councils over the three year recruitment period. This sample provides >90 % power with two-tailed significance of *p* < 0.001 to detect pre-post changes of 60 minutes of physical activity per week, 0.5 serves of fruit or vegetables, 2 kg weight and clinically relevant changes in physical and mental components of quality of life (3 units each) [71], based on assumed standard deviations of change of 300 min/week, 1.5 fruit and 2 vegetable serves, 8 kg weight, and 8 units on the mental and physical component scores. These calculations allow for 30 % participant attrition and adjustment for up to 10 covariates (10 observations per covariate).

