### Economic appraisal

The economic questions associated with this research relate to the costs of implementing HLaC and the relationship between costs, program completion and outcomes. Specifically:*Costs of implementing HLaC:* The fixed costs (i.e., expenditure required to deliver the HLaC program, including resources associated with modifying Cancer Council databases, refining referral pathways, adapting the intervention and evaluation protocols and recruiting and training nurses) will be documented. Dollar values will be attached to these resources using publicly available information such as appropriate salary rates for the time of personnel involved in the above activities and commercial prices for the production of any training materials, etc. Fixed costs will be allocated equally over all participants who consent to participate in HLaC. Variable costs (i.e., those that are proportional to the volume of service provided) will be allocated in proportion to the stage of HLaC reached by individuals [72].*Relationship between costs, completion and outcomes:* Stage of completion will be defined as follows: Stage 1 = completion of ≥3 x weekly phone calls; Stage 2 = completion of Stage 1 + ≥3 x fortnightly phone calls; Stage 3 = completion of stages 1 + 2 + ≥3 monthly calls. For the purposes of the economic appraisal, outcomes will be defined using a series of pre-defined benchmarks based on pre-post program changes in the behavioural and anthropometric variables. For total physical activity, participants who reported achieving 150 minutes/week are considered as having made improvements in their physical activity level. For vegetables and fruit, participants who reported achieving the target of 5 and 2 serves/day, respectively, are classified as having made positive changes in their dietary behaviour. For weight (among participants where weight loss is indicated), those who recorded a body weight reduction at follow-up ≥3 % of their baseline weight will be classified as having successfully achieved a health enhancing benefit [73]. Regression analysis will be used to assess the relationship between completion of stages and outcomes achieved. It is hypothesised that those who complete Stage 3 will have better outcomes than Stage 2 completers who in turn will have better outcomes than those who do not proceed beyond Stage 1. Pre- and post-test differences will be calculated as changes in Quality of Life (SF-12) and Quality Adjusted Life Years (QALYs) SF6D [74] (calculated from SF-12). Data will be analysed with and without imputed outcomes. Sensitivity analysis will be used to explore the impact of varying assumptions about the cut-offs used to define improvements in the secondary outcomes noted above.

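### The ordered stage-of-completion hypothesis is examined only on yes/no cuts of outcomes measured on a full scale; a full-scale regression beside the benchmarks would be a cheap gain in power

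*Protocol article*

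**What the plan says.** The Economic appraisal section of the protocol article defines three stages of completion by the number of weekly, fortnightly and monthly calls completed. It then states: "For the purposes of the economic appraisal, outcomes will be defined using a series of pre-defined benchmarks". Four benchmarks follow, each a yes/no classification: reaching 150 minutes of activity a week, reaching 5 vegetable serves, reaching 2 fruit serves, and (where weight loss is indicated) losing at least 3 % of baseline weight.

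The next step is: "Regression analysis will be used to assess the relationship between completion of stages and outcomes achieved". The hypothesis attached to it is ordered: Stage 3 better than Stage 2, and Stage 2 better than those who stop at Stage 1. On robustness the section says: "Sensitivity analysis will be used to explore the impact of varying assumptions about the cut-offs used to define improvements". It also plans analyses with and without imputed outcomes, and calculates changes in SF-12 and SF-6D QALYs without tying them to stage.

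The Statistical analyses section plans mixed models on the repeated measures for the effectiveness outcomes. It does not describe stage as a term in those models.

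**The concern.** Minutes of activity, serves and weight are all collected before and after the program on their full scale. The benchmarks have a clear use in counting successes and setting them against cost. Nothing in the article requires them as the response variable when the question is whether outcomes improve with stage reached. Cutting discards information within each side of the threshold: a participant who rises from 1 to 4 vegetable serves scores the same as one who does not change. Moving the threshold does not recover that information, so every version of the stage analysis that the article states carries the loss.

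At stake is the chance of seeing a real gradient across stages. The article allocates variable costs by stage reached, so the gradient bears on how cost and outcome are related.

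**Working it through.** **1. The plan's own power figure.** The inputs are from the section on sample size for the secondary outcomes: "a sample size of approximately 900 participants across the four participating Cancer Councils"; "These calculations allow for 30 % participant attrition and adjustment for up to 10 covariates" (10 observations per covariate); changes "to detect pre-post changes of 60 minutes of physical activity per week, 0.5 serves of fruit or vegetables, 2 kg weight"; and "based on assumed standard deviations of change of 300 min/week, 1.5 fruit and 2 vegetable serves, 8 kg weight". The significance level is two-sided 0.001.

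Analysed n = 900 × 0.70 = 630; less 10 × 10 = 100 gives 530. Power = Φ(δ/SD × √n − 3.291).
- Activity: 60/300 = 0.20; 0.20 × √530 = 4.604; Φ(1.314) = 90.5 %.
- Weight and vegetables: 2/8 = 0.5/2 = 0.25; 0.25 × √530 = 5.755; Φ(2.465) = 99.3 %.
- Fruit: 0.5/1.5 = 0.33; about 100 %.

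The stated power above 90 % reproduces. It concerns the pooled pre-post change on the full scale. No power is stated for the stage regression.

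**2. Information kept by a cut.** For a normal outcome with a small shift, the efficiency of the cut relative to the full scale is φ(c)²/[p(1 − p)], where p is the proportion reaching the benchmark and c = Φ⁻¹(p).
- p = 0.50: 0.3989²/0.25 = 0.64
- p = 0.30: 0.3477²/0.21 = 0.58
- p = 0.20: 0.2800²/0.16 = 0.49
- p = 0.10: 0.1755²/0.09 = 0.34

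**3. What that means for power, under stated assumptions.** The article gives none of the following, so each is an assumption:
- 630 analysed;
- Stage 3 against everyone below;
- a between-stage difference equal to the plan's pre-post change;
- the plan's SD of change used as the outcome SD, including for the follow-up levels;
- normal outcomes with equal variances;
- 10–50 % of the lower group reaching the benchmark;
- two-sided 0.05.

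Full scale: power = Φ(d/√(1/n₁ + 1/n₂) − 1.960). Cut: the two-proportion test with p₂ for the lower group, p₁ = Φ(Φ⁻¹(p₂) + d), and a pooled variance under the null.

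Worked case, d = 0.25, 450/180, p₂ = 0.50:
- Full scale: √(1/450 + 1/180) = 0.0882; 0.25/0.0882 = 2.835; Φ(0.875) = 80.9 %.
- Cut: p₁ = Φ(0.25) = 0.599, difference 0.0987; SE 0.0437 under the null and 0.0439 under the alternative; Φ[(0.0987 − 1.960 × 0.0437)/0.0439] = 61.8 %.
- Loss: 19.1 points.

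| Split (Stage 3/rest) | d | Full scale, % | Cut, % (p₂ 10 % to 50 %) | Loss, points |
|---|---|---|---|---|
| 450/180 | 0.20 | 62.1 | 25.7–44.0 | 18.1–36.4 |
| | 0.25 | 80.9 | 38.5–61.8 | 19.1–42.4 |
| | 0.33 | 96.6 | 63.2–85.2 | 11.4–33.4 |
| 315/315 | 0.20 | 70.9 | 33.5–51.4 | 19.5–37.3 |
| | 0.25 | 88.1 | 49.1–70.3 | 17.8–39.0 |
| | 0.33 | 98.7 | 74.7–91.3 | 7.4–24.0 |
| 600/30 | 0.20 | 18.8 | 6.4–14.0 | 4.7–12.3 |
| | 0.25 | 26.7 | 8.2–19.3 | 7.4–18.5 |
| | 0.33 | 42.9 | 12.5–30.8 | 12.2–30.5 |

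With an unpooled variance, the upper ends fall to about 36 points at 450/180 and 19 at 600/30; at 315/315 little changes.

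**4. If the 0.001 level applied here.** The article does not say that it does. The loss would be about 8–56 points at 450/180 and about 1–6 at 600/30, where full-scale power is itself only 1–7 %.

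**The case against.** The benchmarks are not arbitrary. They are introduced for the economic appraisal, the serve targets are the program's own (Table 2), and whether later stages bring more people to target is a fair question to set beside cost by stage. That stands, and is why the benchmarks should stay. It does not make them the best response for testing a gradient.

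The split is uncertain. The Accrual targets section expects about 600–680 completers from 900 enrolled, so 630 is close to the number of completers, and the group below Stage 3 with follow-up data may be small. At 600/30 both analyses are weak, and the full scale would not rescue the comparison. This also stands. The planned analysis with imputed outcomes leaves the effective split unknown.

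The figures cover only Stage 3 against the rest. Stage 2 against Stage 1, probably a smaller contrast, is not computed.

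A reader might go further and infer three things that the article does not support:
- That a definite number of power points is lost. The inputs for such a figure are not given.
- That this is the only planned test of the stage gradient. The article is condensed, its full analysis plan is not shown, and the SF-12 and SF-6D changes are neither tied to stage nor excluded.
- That a null result would be taken to mean that later calls add nothing, or would set the number of calls funded. No text says so. Stage reached is self-selected in a single-group design, so more power gives a sharper association and not a causal answer.

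**Conclusion.** The point holds as a cheap improvement. The article attaches an ordered hypothesis to dichotomised outcomes, its stated sensitivity analysis keeps them dichotomised, and it describes no full-scale analysis by stage. Power was lost in every setting tried, because under normality a cut keeps at most about 64 % of the information. The amount is conditional: about 11–42 points at 450/180, 7–39 at 315/315 and 5–30 at 600/30, all at two-sided 0.05 under the assumptions listed in the working. None of these is a property of the plan as written.

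The reach is limited. The primary outcomes are descriptive, and the power stated for the mixed-model effectiveness outcomes reproduces and is unaffected. What is weakened is one association within the economic appraisal.

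**What to change.** In the Economic appraisal section, test the stage hypothesis by regressing each outcome on its full scale on stage reached: follow-up minutes per week, vegetable serves, fruit serves, and percent weight change where weight loss is indicated. Adjust each for its baseline value and use robust standard errors, since activity and serves are likely to be skewed. Keep the benchmarks, and the sensitivity analysis of their cut-offs, for the proportion of successes and the cost per success. State that stage reached is self-selected and that the result is an association.

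The cost is a change of wording and one extra regression per outcome on data already collected. The small downside is a coefficient in minutes, serves or percent and not in successes, which is why the benchmark proportions should still be reported beside it.

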**Methods/Design:**

Healthy Living after Cancer (HLaC) is a national dissemination and implementation study that will evaluate the integration of an evidence-based lifestyle intervention for cancer survivors into an existing telephone cancer information and support service delivered by Australian state-based Cancer Councils. Eligible participants (adults having completed cancer treatment with curative intent) will receive 12 health coaching calls over 6 months from Cancer Council nurses/allied health professionals targeting national guidelines for physical activity, healthy eating and weight control. Using the RE-AIM evaluation framework, primary outcomes are service-level indicators of program reach, adoption, implementation/costs and maintenance, with secondary (effectiveness) outcomes of patient-reported anthropometric, behavioural and psychosocial variables collected at pre- and post-program completion. The total participant accrual target across four participating Cancer Councils is 900 over 3 years.

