### Accrual targets

The overarching aim is for each Cancer Council to deliver the program over a three-year period. This should afford adequate experience with program implementation and familiarity with outcomes to inform decisions on program sustainability. Accrual targets for each Cancer Council are based on available resources to implement the program. There is capacity for each participating Cancer Council to achieve approximately 50–60 program completions/year implementing the HLaC program 6-month/12 call protocol (refer to the program delivery section). With an estimated 30 % attrition, each Cancer Council would therefore need to enrol approximately 75–80 participants per year. The attrition estimate is based on the high (nearly 50 %) attrition observed in other disseminated lifestyle intervention programs in the general adult population [58, 59], but tempered by the fact that cancer survivors tend to be highly motivated such that cancer-specific trials generally achieve 90 % 12-month retention [32, 35, 52, 53, 60]. Across the three years of HLaC implementation, it is anticipated that each Cancer Council will achieve completion rates of approximately 150–180 participants, for a total of approximately 600–680 HLaC completing (from 900 enrolled) during the proposed study (refer to the sample size section).

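### Three of the economic benchmarks count levels already held at baseline as improvement, so the stage regression, with no baseline adjustment stated, can show a gradient that calls did not cause

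*Protocol article*

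**What the plan says.** All of the following is in the Protocol article, mainly in its Economic appraisal section.

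- **Exposure.** Stage is built from calls completed: at least three weekly calls, then at least three fortnightly calls as well, and finally "Stage 3 = completion of stages 1 + 2 + ≥3 monthly calls".
- **Outcomes.** The section introduces its benchmarks as resting on change between the pre- and post-program assessments. For activity, however, "participants who reported achieving 150 minutes/week are considered as having made improvements in their physical activity level". Vegetables and fruit are handled the same way, at 5 and 2 serves a day. Weight is different: it needs a loss of at least 3 % of the participant's own baseline weight.
- **Analysis.** "Regression analysis will be used to assess the relationship between completion of stages and outcomes achieved". No covariates are named.
- **Hypothesis.** It is directional: "those who complete Stage 3 will have better outcomes than Stage 2 completers who in turn will have better outcomes" than participants who stop at Stage 1.
- **Adjustment elsewhere.** The Statistical analyses section adjusts for predictors of dropout, but says so for the mixed models of the secondary outcomes, not for this regression.

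**The concern.** Two features combine. First, a level at follow-up is labelled as an improvement. The eligibility criteria (Screening and consent) do not require anyone to be below target at entry, so a participant who walked 200 minutes a week before and after the program would be counted as improved. Second, the groups compared are formed after baseline by who keeps taking calls. If people who are more active at entry also stay longer, Stage 3 holds more participants who were at target from the start, and its share of improvers is higher for that reason alone.

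The same section allocates variable costs by stage reached, and the Discussion says the findings will feed into advocacy for sustained funding. A gradient produced by who stays could be read as the return on delivering the later calls.

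**Working it through.** **The plan's own figure.** The only related number is the power for average pre-post change, and it reproduces. The analysable number is 900 × 0.70 = 630, less 10 × 10 = 100 for covariates, giving 530. For activity, 60 / (300/√530) = 4.60; 4.60 − 3.29 = 1.31; power = Φ(1.31) ≈ 90.6 %, against a stated figure above 90 %. This concerns the mean change and does not bear on the comparison of stages.

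**Illustration with no effect of calls.** These inputs are assumptions, not figures in the documents:

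- 45 % are at 150 minutes/week at baseline. This is compatible with the Background, which says more than half of survivors miss activity recommendations.
- 85 % of those at target at baseline, and 30 % of the others, are at target at follow-up, whatever stage they reach.
- Stage 3 is reached by 80 % of those at target at baseline and 60 % of the others; in a milder case, by 75 % and 65 %.
- Everyone is assessed at follow-up.

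The share counted as improved in a group is 0.85 × a + 0.30 × (1 − a) = 0.30 + 0.55 × a, where a is the fraction of the group at target at baseline.

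*80 % v 60 %* (overall 0.45 × 0.80 + 0.55 × 0.60 = 69 %, close to the planned 70 %):

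- Stage 3: a = 0.36 / (0.36 + 0.33) = 0.522; improved = 58.7 %
- Lower stages: a = 0.09 / (0.09 + 0.22) = 0.290; improved = 46.0 %
- Difference: about 13 points

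*75 % v 65 %* (overall 69.5 %):

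- Stage 3: a = 0.3375 / (0.3375 + 0.3575) = 0.486; improved = 56.7 %
- Lower stages: a = 0.1125 / (0.1125 + 0.1925) = 0.369; improved = 50.3 %
- Difference: about 6 points

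In the first case, 0.522 × 0.85 / 0.587 = 76 % of the Stage 3 participants counted as improved were at target before they started. Within each baseline stratum the rates are equal across stages by construction (85 % and 30 %), so conditioning on baseline removes the whole difference.

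**Three-stage simulation with no effect of calls.** It used 400,000 participants, the same gain of 60 minutes/week for everyone and the plan's SD of change of 300. Further assumptions: pre-post correlation 0.5, mean baseline 150 minutes/week, normal outcomes, stages split 15/15/70 %, and follow-up of 10/50/100 % by stage. Odds ratio per stage for reaching 150 minutes/week:

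| Correlation of adherence with baseline activity | Unadjusted | Adjusted for baseline |
|---|---|---|
| −0.2 | 0.84 | 1.01 |
| 0 | 1.00 | 1.01 |
| 0.1 | 1.12 | 1.02 |
| 0.2 | 1.18 | 0.98 |
| 0.3 | 1.28 | 0.98 |
| 0.5 | 1.60 | 1.01 |

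Three further results at correlation 0.2:

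- The rates by stage are 52/55/60 %, and the same with complete follow-up. The gradient here comes from baseline differences, not from missing data.
- Among participants below target at baseline, with complete follow-up, the rates are 40/41/43 %. Restriction shrinks the gradient from 8 to 3 points but does not remove it, so adjustment is needed as well.
- If adherence also tracks progress during the program (correlation 0.1, 0.2 or 0.3 with residual change), the adjusted odds ratio is still 1.21, 1.50 or 1.91.

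**The case against.** Several counter-arguments have force.

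- **A condensed article need not list covariates.** This stands: the silence on baseline adjustment is not an error in itself. What does not fall away is the benchmark wording, which is stated in full and conflicts with its own stated basis. The verb for reaching 150 minutes could be meant as newly reaching it, but the text does not say so, and the two readings classify people already at target differently.
- **The plan speaks of a relationship, not an effect.** True, and the hypothesis only compares groups. It is nonetheless directional and sits in a cost analysis by stage, so the limit on interpretation should be explicit.
- **Safeguards exist.** The plan varies the cut-offs, analyses with and without imputed outcomes, and tests sensitivity to missing-data assumptions. None of these deals with who stays on.
- **Not every outcome is affected.** Weight is relative to baseline, and quality of life and QALYs are pre-post differences.

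A reader might go further in three ways that the documents do not support.

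- *That the gradient is bound to appear.* Nothing in the article says that more active people stay longer. Without that selection the odds ratio is 1.00, and with the reverse it is 0.84.
- *That participants below Stage 3 have no follow-up by the plan's own assumption.* The inference comes from one percentage appearing twice, "With an estimated 30 % attrition, each Cancer Council would therefore need to enrol approximately 75–80 participants per year" and "These calculations allow for 30 % participant attrition", and from outcomes being "behavioural and psychosocial variables collected at pre- and post-program completion". The last phrase gives timing; it does not limit assessment to completers. Table 5 lists program completion and completion of assessments as separate indicators. If those participants truly had no data, the observed-case contrast could not be estimated at all.
- *That imputation would fill the lower stages from completers.* No method is named. Filling from completers would tend to shrink a gradient. Counting missing as failure would create one: 6/29/58 % by stage in the simulation, with no selection on baseline or change.

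**Conclusion.** The point holds in a limited form. The benchmarks for activity, vegetables and fruit contradict the section's statement that they rest on change, and relating them to a self-selected stage can produce the hypothesised ordering with no effect of calls. For activity, the assumed inputs give 6 to 13 percentage points between Stage 3 and lower stages. That size depends on the baseline share at target and on how strongly baseline activity predicts staying, neither of which the documents give. For diet it may be smaller, since the Background puts the share missing dietary guidelines at 90 %. The illustration merges Stages 1 and 2; the three-step ordering is shown only by the simulation. This is one supporting economic analysis, and the primary outcomes and the mixed models are untouched.

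**What to change.** 1. Define the activity, vegetable and fruit benchmarks as change from baseline, or restrict each to participants below that target at baseline.
2. Adjust the stage regression for the baseline value of the same outcome and for the predictors of dropout already planned for the mixed models. Keep this adjustment under either option in item 1: restriction alone leaves some gradient, and change is itself related to starting level.
3. Report the number with observed follow-up at each stage beside every stage contrast, so that readers can see how much rests on imputed outcomes.
4. Present the result as an association between stage and outcome, stating that adjustment does not remove selection on progress during the program.

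No new data are needed, since baseline values are already collected. The cost is slightly more analysis work and, under restriction, a smaller analysis set: with the assumed 45 % at the activity target, 0.55 × 900 = 495 of those enrolled would remain for that benchmark, before attrition.
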